##### Randomization and blinding

After recruitment, randomization will be conducted using the computer random list generated by STATA 15.0 software. A 1:1 ratio of patients will be randomly assigned to the intervention group or the control group. Sealed envelopes containing the group numbers will be kept by the research manager, who is not directly involved in participant recruitment or follow-up. The research designer will keep the group assignment results until the end of the data analysis period (43, 44).

##### Pilot stage

To determine whether the intervention and the trial can be implemented, a political study will be carried out. To test the randomization and recruitment procedures, 30 new pulmonary TB patients – 10 in each district (Chifeng, Hohhot, and Baotou) meeting either an education level ≤ primary school or Mongolian monolingual status – will be recruited and randomized into the intervention or control arm as pilot cases. The feasibility and acceptability of the intervention will then be evaluated after 8 weeks of observation.

During this period, cultural adaptation needs will be assessed. Bilingual (Mandarin/Mongolian) System Usability Scale (SUS) assessments will be conducted at device handover (T0) and after a 2-week adaptation period (T1). Iterative refinements will be implemented through three cycles (2 weeks/cycle), targeting SUS scores ≥ 70. Modifications will focus on pictorial interfaces, audio instructions, and workflow simplification, with all adjustments requiring *κ* > 0.8 inter-rater reliability for problem identification. The implementation plan will be revised based on the pilot study results.

### Societal perspective cost-utility analysis

This economic evaluation adopts a societal perspective incorporating three key cost components: (1) Direct medical costs including EMM procurement and maintenance (with cloud service fees), healthcare personnel training differentiated by urban/rural rates, and outpatient consultations adjusted according to Inner Mongolia’s tiered pricing system; (2) Patient-incurred costs comprising travel expenses calculated as round-trip distance × local transit fare, pastoralists’ fuel costs for private vehicles, and lost herding income quantified via sheep unit equivalents/day with seasonal grazing adjustments; (3) Societal benefits such as averted MDR-TB costs projected over 10 years using WHO-CHOICE unit costs (including indirect costs from transmission interruption), productivity gains measured through the human capital approach applied to employment data, and Quality-Adjusted Life Years derived from EQ-5D-5L surveys at baseline/6/12 months using Chinese health status preference weights. Analytical approaches will report incremental cost-effectiveness ratios for both adherence improvement (ICER) and quality-adjusted life years (ICUR). Sensitivity analyses include discount rate variations (base case 3%, range 0–5%), time horizon scenarios (5/10/20-year projections), probabilistic sensitivity analysis with 10,000 Monte Carlo iterations, and geographic cluster subgroup analyses (Chifeng/Hohhot/Baotou clusters), with all costs standardized to 2025 RMB using China’s CPI health component.

The human capital approach was selected over the friction cost method for productivity loss estimation based on the following considerations: (1) Methodological Appropriateness‌: For chronic conditions like TB requiring long-term therapy (standard 6-month regimen), the human capital approach more comprehensively captures the prolonged productivity losses. This is particularly critical for pastoral patients, since treatment interruption may cause cumulative income impacts spanning several years due to the unique demands of nomadic livelihoods. (2) Research Objective Alignment: As this study aims to assess the comprehensive impact of optimized interventions on patients’ adherence and quality of life, the human capital method better reflects the long-term economic benefits arising from improved treatment compliance. (3) Regional Specificity: In Inner Mongolia’s pastoral regions, TB patients’ mobile lifestyles imply that treatment interruptions can result in sustained negative livelihood impacts over extended periods, which the human capital approach can effectively quantify. (4) Data Feasibility: Friction time, vacancy period, and other key parameters required for the friction cost method are lacking for Inner Mongolia, while employment and wage data essential for the human capital approach are more accessible and verifiable through local statistical sources. (5) International Standards Compatibility: The WHO recommends the human capital approach for economic evaluations in TB, facilitating international comparison of findings and policy implications. (6) Policy Relevance: From a public health decision-making perspective, estimates derived from the human capital approach more accurately reflect the true economic burden of TB on individuals and society in the Inner Mongolian context.

Consequently,‌ to calculate productivity losses ‌using this approach‌, we will source employment data and wage rates for Chifeng, Hohhot, and Baotou from the 2025 data ‌published‌ by the local Bureau of Statistics and the ‌Human Resources and Social Security‌ departments.

### Ethical approval

The Xi’an Jiaotong University Health Science Center’s Ethics Committee granted ethics approval (approval number: 2020–119).

### Data collection

Inner Mongolia CDC will regularly gather patient data, such as name, age, gender, education, occupation, diagnosis, and treatment results. The results of sputum smears performed at the fifth and sixth months, as well as information on conversion at the second month, loss to follow-up, and death, will also be recorded as routinely tracked treatment outcomes (8). The treatment adherence data, collected by the electronic monitors and downloaded from the cloud-based database, will be normalized as percentages of prescribed doses to enable standardized comparisons across patients with varying prescription regimens. To ensure that all missed doses are accurately recorded, we will compare the adherence history obtained from e-monitoring devices with pill counts manually collected at the conclusion of each outpatient visit. Cases with *κ* ≤ 0.6 (indicating device-pill count discrepancies) will trigger qualitative interviews to identify root causes (e.g., device tampering, operational errors, non-adherence), and will be analyzed thematically via NVivo 12.0 per Landis and Koch criteria. Adherence data quality will be further ensured through triple validation‌: (1) Monthly unannounced pill counts (10% participants stratified proportionally across Chifeng, Hohhot, and Baotou populations) with a validity threshold of *κ* > 0.8 (SPSS 28.0); (2) Anti-tampering protocols: Randomized audits + 20 × digital microscopy for blister integrity; (3) Tiered corrections: Device recalibration if 0.6 < *κ* ≤ 0.8; data exclusion followed by root-cause analysis if *κ* ≤ 0.6. While cases with *κ* ≤ 0.6 will undergo root-cause analysis and qualitative interviews to identify potential biases, these cases will remain in the primary Intention-to-treat (ITT) analysis with appropriate statistical handling. Finally, data on implementation costs, such as the number of trainees, the trainers’ labor and travel costs, and the price of the EMM boxes and training materials, will be gathered using the researchers’ work logs. We will implement double entry and examine a representative sample to ensure data entry accuracy.

While stratified random sampling improves validity, two methodological considerations emerge: (1) Potential underrepresentation of mobile populations, adjusted via entropy-weighting with approved anonymized mobility data; (2) Monthly audits could miss short-term adherence variations, mitigated by randomized timing and blister pack integrity checks. The *κ* thresholds follow Landis and Koch but require local context interpretation.

### Statistical analysis

ITT analysis will be performed for the primary analysis, including all randomized participants regardless of adherence data quality or device-pill count discrepancies.‌ For cases with *κ* ≤ 0.6 adherence discrepancies, a three-tier multiple imputation strategy will be implemented to maintain the ITT principle.

The Enhanced Multiple Imputation Procedure for *κ* ≤ 0.6 Cases includes: (1) Level 1 (Baseline and Treatment Patterns) - initial imputation based on observed baseline characteristics (age, gender, education) and treatment assignment status (as fixed covariate); (2) Level 2 (Qualitative Insights) – contextualized imputation incorporating key barriers identified in qualitative interviews (e.g., device tampering, operational errors); and (3) Level 3 (Device and Location Factors) - population-specific imputation considering device types and residence classification (urban/rural). The multiple imputation procedure will use Multiple Imputation by Chained Equations with 20 imputed datasets, using baseline characteristics, treatment assignment status, time variables, and observed adherence patterns. The following variables will undergo imputation: age, gender, education, urban/rural residence type, and monthly adherence rates. Final effect estimates will be obtained by combining results across all imputed datasets using Rubin’s rules.

The Sensitivity Analysis Framework comprises: (1) Primary analysis - ITT analysis including all randomized participants with multiple imputation for missing data; (2) Sensitivity analysis 1 – Complete-case analysis including only cases with *κ* > 0.6 to assess whether the primary ITT results are consistent in the subset of high-quality data (*κ* > 0.6), providing a baseline for comparison with the imputed results for cases with *κ* ≤ 0.6‌; (3) Sensitivity analysis 2 – Household-pairs analysis – This analysis examines adherence trajectories using shared random intercept models, specifically for cohabitating patient pairs (non-immediate family members) with device-recorded versus pill-count adherence agreement *κ* > 0.8; (4) Sensitivity analysis 3 – Bayesian analysis using Markov chain Monte Carlo methods with appropriate prior specifications to evaluate the influence of prior distribution choices on posterior effect estimates‌; and (5) Sensitivity analysis 4 - Bootstrapped confidence intervals (1,000 iterations) for cases with *κ* ≤ 0.6 adherence discrepancies to validate the robustness of the multiple imputation approach under different statistical paradigms.

Covariate-adjusted analyses‌ will be used for all outcomes, with individual consideration of participant clustering in community health centers and township hospitals. Treatment adherence will be analyzed as a continuous variable (percentage) while maintaining the predefined categorization threshold of ≥ 80% for high adherence versus < 80% for non-adherence. Intervention-control group differences will be compared using *t-*tests and 
$\chi^{2}$
 tests (20). Intervention effects will be examined using generalized estimating equation (GEE) models incorporating spatial autocorrelation terms to quantify contamination effects, with sensitivity analyses comparing: (1) Household-clustered GEE models using household IDs as clustering variables with exchangeable correlation structure, adopting an intraclass correlation coefficient threshold < 0.1 based on Inner Mongolia’s low population density (20.19 persons/km^2^) and *κ* weak consistency standards (0–0.2); and (2) Bootstrapped confidence intervals (1,000 iterations) for cases with *κ* ≤ 0.6 adherence discrepancies (8).

Cases with *κ* ≤ 0.6 will be evaluated via bootstrapped confidence intervals (1,000 iterations) and qualitative contextualization. These cases remain included in the primary ITT analysis. For continuous outcomes, mean differences and standardized mean differences will be used to assess intervention effectiveness. For binary outcomes, odds ratios and risk differences will be calculated. Additionally, a mixed-effects model that allows health facility-level estimates to be random effects and accounts for facility- and time-level clustering will be used to compare pre- and post-intervention proportions for reach and adoption (20). Implementation and maintenance will be evaluated using a thematic analysis methodology, to identify emerging themes. The data will be translated, transcribed, verified‌, cleaned, and then analyzed using NVivo 12.

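### Sensitivity analysis 4 bootstraps only the kappa ≤ 0.6 cases, so it cannot test the imputation assumption it is meant to validate, and no other listed sensitivity analysis allows missing not at random

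*Protocol article*

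**What the plan says.** All points are in the protocol article, Statistical analysis section, unless stated otherwise.

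- **Imputation.** The primary ITT analysis keeps patients with kappa ≤ 0.6 and imputes for them using "Multiple Imputation by Chained Equations with 20 imputed datasets, using baseline characteristics, treatment assignment status, time variables, and observed adherence patterns". Level 2 is described as "contextualized imputation incorporating key barriers identified in qualitative interviews (e.g., device tampering, operational errors"), and Level 3 adds device type and residence. "Final effect estimates will be obtained by combining results across all imputed datasets" by Rubin's rules.
- **Sensitivity analysis 4.** "Bootstrapped confidence intervals (1,000 iterations) for cases with" kappa ≤ 0.6, with the stated aim "to validate the robustness of the multiple imputation approach under different statistical paradigms". The section later repeats that these cases "will be evaluated via bootstrapped confidence intervals (1,000 iterations) and qualitative contextualization".
- **Sensitivity analysis 1.** Only cases with kappa > 0.6, "to assess whether the primary ITT results are consistent in the subset of high-quality data".
- **Sensitivity analysis 2.** "This analysis examines adherence trajectories using shared random intercept models, specifically for cohabitating patient pairs" with kappa > 0.8.
- **Sensitivity analysis 3.** A Bayesian analysis that varies the priors. A household-clustered GEE is also listed as a comparison.
- **Data collection section.** Root causes of discordance may include tampering, operational errors and non-adherence.
- **Follow-up study section.** Participants with kappa ≤ 0.6 receive a separate bias analysis on baseline characteristics.

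**The concern.** The article assigns a specific analysis to a specific job, and the analysis cannot do that job. A bootstrap measures how an estimate varies from sample to sample. If it resamples imputed values, it inherits the imputation model. If it resamples the discordant device values, it inherits their measurement error. In neither case does the assumption behind the imputation change.

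That assumption matters here. Chained equations conditional on observed variables imply missing at random, although the article does not name it. If non-adherence is one reason why device and pill count disagree, being flagged may depend on the value that is being imputed. The optimized programme also changes the interface, the audio prompts and device access in one arm, so both the share flagged and the reason for flagging could differ by arm. The trial could then describe its imputation as validated on the strength of a check that is insensitive to the failure most worth checking.

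**Working it through.** **1. What each listed analysis varies**

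| Analysis | Flagged patients (kappa ≤ 0.6) | What it varies |
|---|---|---|
| Primary | imputed from observed data | – |
| Sensitivity 1 | dropped | analysis set |
| Sensitivity 2 | outside the set (kappa > 0.8 pairs) | random-effect structure |
| Sensitivity 3 | no change stated | priors on the effect |
| Household GEE | no change stated | clustering unit |
| Sensitivity 4 | resampled alone | sampling variability |

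No row shifts the flagged patients' adherence away from what the observed data predict.

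**2. The article's own power figure**

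Inputs from the Sample size section: 300 patients, 40% against 28% monthly non-adherence, six outcomes, correlation 0.5, alpha 0.05 (two-sided assumed). The variance factor is (1 + 5 × 0.5)/6 = 0.583. The effective n per arm is 150/0.583 = 257, which gives power 82.1% against the stated 81.5%. The figure reproduces. It contains no facility clustering. The point does not depend on it; it only supplies a variance for step 3.

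**3. Illustrative scale**

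The flagged shares below are assumptions, because the documents give none. The calculation uses the dichotomised monthly outcome and ignores between-imputation variance.

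SE = √[(0.40 × 0.60 + 0.28 × 0.72) × 0.583 / n per arm] = √(0.2576/n).

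- Arm difference within the flagged subset, 10% flagged (n = 15): SE 0.131, half-width 1.96 × 0.131 = 26 points.
- Same, 20% flagged (n = 30): SE 0.093, half-width 18 points.
- Full trial (n = 150): SE 0.0414, so significance needs 1.96 × 0.0414 = 8.1 points.

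If the observed effect is 12 points and only one arm's flagged patients are shifted, the conclusion changes at (12 − 1.96 × SE × √D)/share, where D is an assumed design effect for facility clustering:

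| D | Points needed for significance | Shift at 10% flagged | Shift at 20% flagged |
|---|---|---|---|
| 1.0 | 8.1 | 39 | 19 |
| 1.5 | 9.9 | 21 | 10 |
| 2.0 | 11.5 | 5 | 3 |

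**4. Would the listed checks signal a departure?**

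Simulation with assumed inputs: 600 trials per scenario, 150 patients per arm, continuous adherence with residual SD 15, a 5-point arm difference before discordance, 20 imputations under missing at random, and 300 bootstrap resamples of the flagged cases' imputed values. There is no facility clustering, and the imputation uses no interview barriers. The gap is how far flagged patients fall below what missing at random predicts. True effect = 5 − (share × gap in intervention − share × gap in control).

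| Flagged, control/intervention | Gap, control/intervention | True effect | Imputation estimate (coverage) | Complete-case estimate | Bootstrap interval contains imputation estimate |
|---|---|---|---|---|---|
| 20%/20% | 0/0 | 5.0 | 4.9 (96%) | 4.9 | 94% |
| 20%/20% | 15/15 | 5.0 | 4.9 (97%) | 4.9 | 88% |
| 15%/15% | 10/30 | 2.0 | 4.9 (65%) | 5.0 | 91% |
| 20%/20% | 10/30 | 1.0 | 5.1 (47%) | 5.1 | 89% |
| 10%/20% | 20/20 | 3.0 | 5.0 (80%) | 5.0 | 91% |
| 10%/30% | 20/20 | 1.0 | 5.1 (47%) | 5.1 | 91% |

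The last column barely moves between the unbiased rows (first two) and the biased rows (last four). The complete-case estimate follows the imputation estimate to within 0.02. Neither check separates a sound imputation from a biased one.

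**The case against.** **The bootstrap may have a narrower purpose.** Its reference to different paradigms can be read as comparing Rubin's-rules intervals with resampling intervals, and its second mention sits beside the GEE models. That is a legitimate use, but it concerns interval width and would need the full ITT set. The article also never says that the bootstrap estimates an arm difference within the flagged subset, so the 26- and 18-point half-widths apply only on that reading.

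**The plan has safeguards.** Level 2 feeds tampering and operational errors into the imputation, pill counts give a second adherence measure, interviews seek root causes, and the Follow-up study section plans a baseline bias analysis. These make the imputation more plausible. None of them varies its assumption, and a comparison of baseline characteristics cannot reveal a dependence on the unobserved adherence itself.

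**A tipping-point analysis may sit in an unseen SAP.** This is fair, and its absence from an article would not be a finding on its own. What stands is that the article itself gives the validating role to an analysis that cannot fill it.

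**Stronger readings a reader might infer.** One is that no planned analysis departs from missing at random. The documents do not support that: the complete-case analysis already rests on a different assumption. Another is that the primary result is biased. That does not follow either: with equal shares and equal gaps the arm difference was unbiased (4.9 against 5.0).

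**Conclusion.** The point holds in a limited form. Sensitivity analysis 4, as described, cannot test the imputation assumption, and it addresses a post-randomisation subset instead of the ITT effect. None of the listed sensitivity analyses allows flagged patients' adherence to be missing not at random. The primary ITT analysis itself is not shown to be wrong; what fails is the validation claimed for it.

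The size is illustrative only. Under the assumptions in the working, the shift in one arm that would overturn a 12-point result ranges from about 39 points (10% flagged, no facility clustering) to about 3 points (20% flagged, design effect 2.0). A reader might take 39 points as evidence that the result is robust, or a small value as evidence that it is fragile. The documents support neither, because they give no flagged share and no facility-level correlation, and they also plan to analyse adherence as a continuous percentage. Bias in the arm difference requires a departure or a flagged share that differs by arm. The changed interface and prompts make that plausible, but nothing in the documents establishes it.

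**What to change.** Replace Sensitivity analysis 4 with delta-adjusted (tipping-point) multiple imputation on all randomised patients. Shift the imputed adherence of kappa ≤ 0.6 cases separately by arm over a range stated in advance, and report where the conclusion changes. Report the flagged share by arm beside it.

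If a bootstrap is kept, run it on the full ITT set, resample the unit of randomisation, repeat the imputation within each resample, and describe it only as a check of the Rubin's-rules interval. The unit must be settled first: the Phase 3 Study design section randomises facilities, whereas the Randomization and blinding section assigns patients.

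Amend the later sentence that repeats the bootstrap for the kappa ≤ 0.6 cases to match. The change needs no new data and swaps one sensitivity analysis for another of similar effort.

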##### Outcomes

The primary study hypothesis is that the optimized EM program will result in higher rates of treatment adherence than standard care. As a result, for TB patients, treatment adherence will be the main result. Treatment adherence will be calculated as the percentage of prescribed doses actually taken by the patient each month. The formula is: ‌Treatment Adherence (%) = (Number of doses actually taken / Number of prescribed doses) × 100%‌. For example, if a patient is prescribed 30 doses per month and actually takes 25 doses, their treatment adherence would be (25/30) × 100% = 83.3%. Adherence will be dichotomized as high adherence (≥80% of doses taken) or non-adherence (<80%). The secondary outcomes for TB treatment will be (1) the treatment completion rate, (2) loss to follow-up rate, (3) treatment failure, and (4) death, as defined by the WHO standard definitions (8, 40). Based on the RE-AIM framework, the impact of the optimized EM program will also be assessed in comparison to standard care for the subsequent secondary outcomes (reach, effectiveness, adoption, implementation, and maintenance) (41, 42). For cases with *κ* ≤ 0.6, Phase 1 qualitative findings will inform the “implementation” and “maintenance” RE-AIM domains to address adherence barriers and enhance sustainability. Table 1 provides additional outcome information. Table 1.

**Table 1 tab1:** Outcomes, indicators, and indicator definition by RE-AIM framework.

Outcome	Indicator	Indicator definition
Service outcome	Treatment adherence	Percentage of prescribed doses actually taken each month
Patient outcome	Treatment completion rate	A TB patient who finished treatment without having evidence of treatment failure, but who did not have negative sputum smear or culture results in at least one prior instance or in the final month of treatment, either because the tests were not conducted or the results were not available
	Loss to follow-up rate	A TB patient who did not initiate treatment or whose treatment was interrupted for two consecutive months or more
	Treatment failed	A TB patient who received treatment and had positive results from a sputum smear or culture at month five or later
	Died	A TB patient who passed away before starting treatment or while receiving it, for any reason
Implementation outcome	Reach	Patient-level coverage among all eligible incident TB cases in the catchment area

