However, this study confronts five challenges. First, economic analyses may systematically underestimate three components: (1) informal caregiving burdens; (2) TB transmission externalities; and (3) intergenerational educational impacts. Second, despite employing gold-standard cluster-randomized controlled trials (20) with 20-km contamination buffers, residual risks persist through two primary pathways: (1) offline medication-sharing networks; (2) transient mobility events below the 20-km detection threshold. ‌Notably, low population density (20.19/km^2^ in Inner Mongolia) may mitigate contamination risks from such mobility events. Third, confounding factors, bias, and temporal trends could limit the validity of the findings. Fourth, while AHP-optimized strategy prioritization enhances rigor, the weight allocation might reflect evaluators’ professional biases. Furthermore, although many TB patients in Inner Mongolia lack literacy, they can still use smartphones and WeChat (48), because (1) contacts in WeChat can be identified by icons and (2) WeChat enables smartphones to send audio and video recordings rather than just text. A family member with strong literacy will also be used to teach the TB patient how to use WeChat.

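### The primary outcome is put on two scales with no ranking of scale, test or effect measure, and the t- and chi-square tests listed for comparing arms cannot reflect facility clustering

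*Protocol article*

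**What the plan says.** All places are in the Protocol article.

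- **Outcomes** names adherence as the main result and defines it thus: "Treatment adherence will be calculated as the percentage of prescribed doses actually taken by the patient each month". It then adds: "Adherence will be dichotomized as high adherence (≥80% of doses taken) or non-adherence (<80"%). Table 1 lists only the monthly percentage.
- **Sample size** works with binary monthly non-adherence: 40% in controls, a 12-point improvement, six outcomes per patient, correlation 0.5, 300 patients and 81.5% power. The model is a GEE with month and treatment group.
- **Statistical analysis** puts the outcome on the other scale: "Treatment adherence will be analyzed as a continuous variable (percentage) while maintaining the predefined categorization threshold". The next sentence, "Intervention-control group differences will be compared using", names t-tests and chi-square tests. The one after it says: "Intervention effects will be examined using generalized estimating equation (GEE) models incorporating spatial autocorrelation terms to quantify contamination effects". The section also gives mean difference, standardised mean difference, odds ratio and risk difference. The primary analysis is defined only as intention-to-treat with multiple imputation.
- **On clustering**, Statistical analysis promises covariate-adjusted analyses of all outcomes "with individual consideration of participant clustering in community health centers and township hospitals". The main GEE names no clustering unit. Among its sensitivity analyses are "Household-clustered GEE models using household IDs as clustering variables with exchangeable correlation structure", with an ICC threshold below 0.1 that is justified by regional population density and a kappa agreement band.
- **On the randomisation unit**, the Phase 3 Study design names community health centres and township hospitals, whereas Randomization and blinding allocates patients 1:1.

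**The concern.** A trial needs one primary estimate and one p-value, fixed before outcome data are seen by arm. Here the binary and the continuous scale both have a claim, and each can be tested without adjustment or by GEE. Success could be declared on whichever combination is favourable.

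The second issue is internal consistency. A plain t-test or chi-square test has no term for facility, so it cannot deliver the clustering adjustment that the same section promises for all outcomes. The text does not restrict these tests to baseline or descriptive use. If facilities are randomised, such a test understates the standard error of the arm difference and rejects a true null too often.

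**Working it through.** **Inputs from Sample size.** Control rate 0.40, intervention rate 0.28 (a 12-point improvement), 300 patients (150 per arm), six months, correlation 0.5, no missing data, alpha 0.05. Two-sided testing is assumed, because sidedness is not stated.

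**Assumed inputs.** Facility ICC 0.01 to 0.10 and 5 to 30 patients per facility. The article gives no facility ICC, number of facilities or facility size.

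**Step 1: reproduce the stated power.** Averaging six exchangeable months multiplies the variance by (1 + 5 × 0.5)/6 = 0.583, so the effective number per arm is 150/0.583 = 257.1.

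- Null SE = √(2 × 0.34 × 0.66/257.1) = 0.0418.
- Alternative SE = √((0.24 + 0.2016)/257.1) = 0.0414.
- Power = Φ((0.12 − 1.96 × 0.0418)/0.0414) = 82.1%.

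A Wald test on the logit scale gives 81.6%. Simulation of a binary GEE with patient-level robust variance (4,000 runs, no facility effect) gives 81.3%, with type I error 4.8%. The stated 81.5% is reproduced. Alternatives that do not fit are a single binary outcome per patient (59.3%), one-sided testing (89.2%) and 40% against 52% (78.1%). The 300 patients therefore rest on the monthly binary scale.

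**Step 2: unadjusted test, one value per patient, facilities randomised.** The ignored variance factor is f = 1 + (m − 1) × ICC, where m is patients per facility and the ICC is between patient-level values. Type I error = 2 × (1 − Φ(1.96/√f)). For example, with m = 10 and ICC 0.10, f = 1.9 and 1.96/√1.9 = 1.42, which gives 15.5%.

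| ICC | m = 5 | m = 10 | m = 30 |
|---|---|---|---|
| 0.01 | 5.5% | 6.0% | 8.4% |
| 0.05 | 7.4% | 10.4% | 21.0% |
| 0.10 | 9.8% | 15.5% | 32.1% |

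**Step 3: chi-square on patient-months treated as independent, no facility effect.** f = 1 + 5 × 0.5 = 3.5. Type I error is 2 × (1 − Φ(1.96/√3.5)) = 29.5% by formula and 30.7% by simulation.

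**Step 4: both scales tested at 5%.** This is a simulation under no effect with 150 per arm and an assumed adherence distribution, without clustering. The t-test on mean adherence was significant in 5.0% of runs, the chi-square test on at least 80% adherence in 6.1%, and at least one of them in 8.5%.

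**Step 5: what clustering does to power.** Now take the ICC between monthly observations of different patients in one facility. The variance factor is (3.5 + 6 × (m − 1) × ICC)/6. With m = 10 and ICC 0.01 it is 4.04/6 = 0.673, and power with 300 patients is about 76%. With ICC 0.05 it is 6.2/6 = 1.033, and power is about 58%.

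**The case against.** The best defence is that the plan already has a sound main method. Intervention effects are assigned to GEE, the sample size uses GEE, and facility clustering is expressly mentioned. The t- and chi-square tests could be simple side comparisons. Link function, working correlation and small-sample correction can reasonably sit in a fuller document. All of that stands, and it rules out several stronger readings that a reader might infer:

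- **That the main p-value is invalid.** This follows only if it comes from the unadjusted tests, and no section says so.
- **That facility clustering is left out.** It is promised. What is missing is a named clustering unit for the main GEE.
- **That household is the main clustering level.** The household GEE is listed as a sensitivity analysis. Cohabiting friends, roommates and distant relatives remain eligible, so it has a target.
- **That months will be pooled as independent.** The unit of the t- and chi-square tests is not stated. With one value per patient, repeated months cause no inflation.
- **That an ICC of 0.1 is accepted for facilities.** The threshold is attached to households, so applying it to facilities of 10 patients misreads it.
- **That the density figure is contradicted.** The Setting section gives 2.72 million/27,768 km² = 98 per km² for Baotou and 4.04 million/9,000 km² = 449 per km² for Chifeng. Both areas are stated as minima, so these are upper values. The 20.19 per km² is a figure for the whole region: "Notably, low population density (20.19/km^2^ in Inner Mongolia) may mitigate contamination risks from such mobility events". City and regional densities may differ.

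The defence does not answer the two scales without a ranking, or the conflict between plain tests and the promised clustering adjustment. Those are statements in the article itself, not details deferred elsewhere.

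**Conclusion.** The point holds in this form: the primary outcome has two scales, several tests and four effect measures with no hierarchy, and the unadjusted tests listed for comparing arms conflict with the section's own clustering statement. The sample size supports only the monthly binary GEE.

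The size is conditional. If the main p-value were taken from an unadjusted test on one value per patient, type I error would be about 6% to 16% at 10 patients per facility, and 5.5% to 32% over 5 to 30 patients per facility. This assumes facility randomisation and a patient-level facility ICC of 0.01 to 0.10. It would be about 30% only if months were pooled. The 8.5% for testing both scales rests on an assumed adherence distribution. If patients are randomised individually, the facility inflation does not apply in full, which is one reason why the two statements of the randomisation unit must be reconciled.

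The ICC threshold in the household model is also unsupported: neither population density nor a band for rater agreement says what ICC is tolerable.

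**What to change.** 1. Name one primary analysis: monthly binary non-adherence (below 80%), by GEE with arm and month, one stated effect measure, and robust variance clustered on the randomised unit. If that unit is the facility, add a small-sample correction should facilities be few.
2. Make the continuous percentage a secondary outcome under the same clustering.
3. Label the t-tests and chi-square tests descriptive only.
4. Remove the ICC threshold of 0.1 and its justification from the household sensitivity model. The model itself can stay.
5. Reconcile the Phase 3 Study design with Randomization and blinding on what is randomised.

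These are changes of wording and should be settled before outcomes are examined by arm. The cost is wider confidence intervals and, if facilities are randomised, lower real power than the stated 81.5%, as Step 5 illustrates.
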